#### Sociodemographics and Covariates

To describe the characteristics of the participants, we will collect information about their age and gender. To explore possible covariates or moderators of the intervention effect, we will collect data on body weight, height, stage of change, and clinic type (outpatient or inpatient) and monitor intervention use (number of completed challenges and self-reported success of each challenge).

#### Experience and Feasibility Measures

Once the study is complete, patients’ perspectives will be gathered during short semistructured interviews. The interviews will focus on participants’ experiences with the SCIPP app, possible points of improvement, and their perceived effectiveness of SCT. This information will be used to optimize digital SCT training as well as understand the feasibility of using SCED methodology in people with SMI.

### Procedure

Participants will be visited by a member of the research team 1 day before the start of the experiment. The researcher will help the patient install all necessary apps on the patient’s mobile phone. Next, the researcher will fit the accelerometer to the patients’ hip or belt and demonstrate how to take it off. Finally, the researcher will help participants fill out the baseline questionnaires.

During the baseline phases, physical activity and self-control will be monitored, but no interventions will be administered. To monitor physical activity, the patient will wear the accelerometer each day from 9 AM to 11:59 PM except when sleeping or during activities that involve water, such as showering or swimming. To measure daily self-control, they will be prompted to fill out a morning survey between 11 AM and 1 PM and an evening survey between 7 PM and 9 PM. Reminders for both surveys will be sent after 30 and 60 minutes.

At the start of intervention phase B, the researcher will visit the patient and help set up Google Fit by entering their activity goals (number of steps and number of Heart Points), wake-sleep schedule, weight, and height. Next, the researcher will demonstrate where to find and how to use the primary functions of Google Fit. This will enable patients to self-monitor their activity and receive personalized coaching. During the withdrawal phases of SCED II, the researcher will also deactivate the SCT app and explain to the patient that this app will not be used for the next phase.

At the start of intervention phase C, the researcher will visit the patient and help set up SCIPP by entering the personal goal and dominant hand. The researcher will also inquire about their experiences with participation so far and provide additional instructions regarding Google Fit, the accelerometer, or Ethica, if required. The next day, the patient will receive the first self-control challenge and continue to receive and complete challenges throughout the phase. The researcher will return every 7 days to answer questions and, if necessary, reset the app to extend use up to 28 days until the phase is completed.

Follow-up follows the same procedure as the baseline phases. The researcher will visit the patient to disable all apps on the patient’s phone except Ethica, which is used for data collection. Once the study is completed, the researcher will make a final visit to collect the accelerometer and reactivate any apps that the patient wishes to continue using. In SCED I, the researcher will also conduct the postintervention interview during this visit.

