### Randomization and Blinding

We will randomly assign participants to different baseline, intervention phase B, and follow-up durations in SCED I. All are drawn a priori using the web-based random number generator Research Randomizer [45] with the restriction of having at least 5, 7, and 28 baseline observation days, respectively. In SCED II, phase length will not be randomized as the optimal intervention length will be derived from SCED I. Phase order will not be randomized in both experiments as we are interested in the additive effect of SCT over Google Fit only.

Owing to the nature of the intervention, in which apps are used by participants, it is not possible to blind participants to the phase. The researchers responsible for supporting participants in transferring between phases will not be blinded to the phase for the same reason. Where possible, researchers only involved in data entry, processing, and analysis will be blinded to the phase to improve the reliability of the findings [36].

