*Immediacy* compares the extent to which the level, trend, and variability of the last and first 3 data points of subsequent phases are discriminably different. In SCED I, immediacy is used to examine whether SCT effects are immediate or cumulative and to make decisions about the appropriate phase length in SCED II. Finally, *consistency* involves examining whether data patterns (level and trend) are consistent in phases with the same condition, where more consistent patterns provide greater certainty for a causal relationship between the intervention and outcome. This will be used in SCED II to examine whether physical activity reaches similar level and trend effects in both B phases (Google Fit only) and both C phases (Google Fit+SCT).

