### Strengths and Limitations

A major strength of this study is the combination of 2 approaches to SCED: the multiple-baseline design across participants and the introduction/withdrawal design. The first experiment will allow us to demonstrate whether mobile SCT is effective, for whom it may be most effective, and for how long it should be offered for optimal effects. In addition, the qualitative interviews provide insights into how to optimize the mobile SCT app as well as insights into participation in an extensive longitudinal study from the perspective of people with SMI. This knowledge will be directly applied to the second experiment, in which the optimized intervention will be offered to a new set of patients to validate these findings.

Second, the study also uses accelerometry to assess the physical activity of people with SMI objectively. The use of accelerometry data substantially improves the reliability, validity, and level of detail of data on sedentary behavior and physical activity compared with often-used self-reports in which physical activity levels are consistently overestimated [91-93].

The main limitation is that there is no certainty that people with SMI will persist in SCT, faithfully wear the accelerometer, and provide answers to the daily questionnaires for the considerable study duration of 7 weeks. Nonadherence is a major challenge for any longitudinal study, including N-of-1 designs such as SCED [94]. However, it is specifically challenging in people with SMI [95], and studies suggest that low self-control may also further contribute to low adherence [96]. As this study is both longitudinal and will target individuals with SMI (who commonly have lower self-control than the general population [97]), nonadherence may thus be expected. To address this limitation, we will take additional measurements to avoid complete loss of data (eg, 2 daily measures of self-control instead of 1), schedule regular phone calls and visits by the researcher, and offer financial incentives for continued participation in the study, all strategies associated with better adherence [98-100]. Explicitly reporting on the success of these strategies both from a quantitative (eg, use data) and qualitative (eg, patient interviews) perspective will also help other researchers make more informed decisions about the design of SCED studies specifically in the population with SMI.

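### In SCED I, Google Fit re-instruction given at the visit that starts SCT cannot be separated from the SCT effect in participants who receive it

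*Protocol article*

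**What the plan says.** Randomization and Blinding states the target of the design: "we are interested in the additive effect of SCT over Google Fit only". That makes B versus C the key contrast.

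Procedure gives phase B one described visit, at its start, where Google Fit is set up and "the researcher will demonstrate where to find and how to use the primary functions of Google Fit". No further check inside phase B is described. The next described visit opens phase C. There the researcher sets up SCIPP, asks how participation has gone so far, and will "provide additional instructions regarding Google Fit, the accelerometer, or Ethica, if required". SCT then begins almost at once: "The next day, the patient will receive the first self-control challenge". During phase C, "The researcher will return every 7 days to answer questions and, if necessary, reset the app to extend use up to 28 days".

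Under Visual Analysis, the immediacy check is the one that "compares the extent to which the level, trend, and variability of the last and first 3 data points of subsequent phases are discriminably different". The level term of the piecewise regression is read as the instant and constant effect of the intervention. Under Sociodemographics and Covariates, the intervention-use data named are SCIPP challenges; Google Fit use is not among them.

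Strengths and Limitations adds that the team will "schedule regular phone calls and visits by the researcher", without assigning these contacts to phases.

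**The concern.** To isolate what SCT adds, Google Fit has to be delivered in the same way in B and in C. The procedure instead places the described opportunity to find and correct Google Fit difficulties on the phase boundary. A participant who struggled with Google Fit in phase B would then start using it properly at the moment SCT starts, and the late Google Fit effect would be credited to SCT.

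There is a knock-on effect. Immediacy in SCED I is to inform the phase length in SCED II, so a false immediate step could also distort that choice. With no Google Fit use data named, the problem would be hard to examine afterwards.

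**Working it through.** The plan states no figure on this point, so there is nothing to reproduce. The question is whether the two effects can be told apart.

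**Inputs from the article.** SCED I: phase B at least 7 days, phase C at least 28 days (Table 1); PLM terms intercept, trend, level and slope; visit content from Procedure. Every effect size below is an assumption.

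**1. One participant, SCED I (B = 7, C = 28 days).** Write y(t) = b0 + b1·t + b2·C(t) + b3·C(t)·(t − 8) + d·R(t), where C = 1 from day 8 and R = 1 from the day of re-instruction. If re-instruction falls at the C start, R equals C on every day. The design matrix has rank 4 of 5, and only the sum b2 + d can be estimated. The first challenge comes one day after the visit, so at most a single day per participant could separate the two.

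**2. Staggered starts.** Six pooled participants with own intercepts and assumed B lengths of 7 to 12 days: rank 9 of 10. R still equals C within each participant.

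**3. Where the step goes.** With a true SCT effect of 0 and an assumed re-instruction step of 1 SD, 2000 simulated series gave a mean level estimate of 0.99 SD. The expected value is b2 + d = 0 + 1 = 1 SD, so the whole step is credited to SCT. Tau-U adjusts for the earlier phase's trend, not for a step at the boundary. Immediacy compares exactly the points on either side of it.

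**4. Illustrative size.** Let Google Fit raise activity by g when used properly, let p be the share of phase B with proper use, and assume full correction at the C start and no SCT effect. Phase means then differ by (1 + g)/(1 + p·g) − 1.

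| g | p = 0 | p = 0.5 | p = 1 |
|---|---|---|---|
| 5% | 5% | 1.05/1.025 − 1 = 2.4% | 0 |
| 10% | 10% | 1.10/1.05 − 1 = 4.8% | 0 |
| 20% | 20% | 1.20/1.10 − 1 = 9.1% | 0 |

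**5. SCED II (assumed 7-14-7-14 days; intercept, C and re-instruction step only).** A gain that persists from the first C phase onward is separable (rank 3 of 3), because the second B phase carries it without SCT. A gain confined to the C phases is not (rank 2 of 3).

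**6. Accelerometer wear.** The article does not say whether counts are divided by worn hours. If they are, and the hourly rate is constant, longer wear changes the outcome by 0%. With an assumed fixed 15-hour denominator, wear rising from 9 to 12 hours gives 12/9 − 1 = 33%, from 7 to 9 hours 29%, and from 12 to 13 hours 8%.

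**7. Re-instruction moved into phase B.** If it takes effect on day 4 of B, the matrix in step 1 has full rank (5 of 5). The step must then be modelled. Left out, a unit step from day 4 gives phase B a mean of 4/7 and a slope of (0 + 1 + 2 + 3)/28 = 6/28. The value projected to day 8 is 4/7 + 4 × 6/28 = 10/7, and the level term is off by 1 − 10/7 = −0.43 of the step. The last three B points (days 5 to 7) all lie after the correction, so immediacy is unaffected.

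**The case against.** The strongest case against is that this is a conditional co-intervention of unknown frequency. Google Fit was chosen as user-friendly and likely suited to this group, and its functions are demonstrated at the start of phase B. SCED I claims only initial effectiveness, its PLM also estimates a slope in which a gradual SCT effect would show, and SCED II is there to validate the result. All of this is fair and limits the weight of the point. None of it removes the coincidence at the C start in SCED I.

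Four stronger readings are tempting and are not supported:

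- A reader might infer that phase C gets much more contact than phase B. The visits opening B and C are 7 days apart when B lasts 7 days, as in SCED II, and at least 7 days apart in SCED I. That is close to the weekly rhythm of phase C.
- A reader might infer that problems can surface only at the phase C visit. The regular calls are not tied to a phase, and the survey platform shows data in real time so that errors can be found.
- A reader might infer that better wear inflates the contrast. The outcome is a rate, and with worn hours as denominator this route largely disappears.
- A reader might infer that both experiments are equally affected. In SCED II, SCT is withdrawn in the second B phase while a lasting gain in Google Fit use would remain, and the consistency check compares the two B phases.

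Nor does it follow from the general remarks on cognitive deficits that many participants will need re-instruction. The article gives no rate.

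**Conclusion.** The point holds for SCED I, for participants whose Google Fit use is corrected at the visit that opens phase C. In them, a step from re-instruction and a step from SCT are one estimate, and neither the planned analyses nor the staggered starts can split it. The size of the bias is unknown; the percentages above rest on assumed Google Fit effects and on full correction at the C start. The wear route is secondary and depends on an unstated denominator. In SCED II the problem is smaller, because a lasting gain can be seen there in part. The plan should be changed, since the remedy is cheap and protects the main contrast, but the design as a whole is not undermined.

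**What to change.** - **Move the check forward.** Check Google Fit, accelerometer and survey use, and re-instruct where needed, at a fixed early point in phase B, for example by phone on day 2 or 3. Check the accelerometer and survey early in phase A. Both fit within the regular calls already planned.
- **Keep helping at the phase C visit.** Withholding help there would risk losing data in an experiment of six people, where nonadherence is the stated main limitation.
- **Log and report.** Record the date and content of all technical help and report it by phase, together with wear time. Where re-instruction on Google Fit took place inside phase B, enter the logged date in the PLM as its own step.
- **Sensitivity analysis.** Repeat B versus C without participants who were re-instructed on Google Fit at the C start, or flag their contrast as confounded.
- **Participants already enrolled.** The Results section reports six included by March 2023, the full size of SCED I. For SCED I participants already enrolled, apply the logging, flagging and sensitivity analysis as far as records allow.

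The cost is one or two short contacts per participant and a log. The drawbacks are a little more contact early in phases A and B, and fewer cases in the sensitivity analysis.

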### Data Analysis

#### Overview

Data analysis will include both visual and supplementary statistical analyses of the time-series data for both SCED I and II [36,42]. Data analysis will be performed using Microsoft Excel (Microsoft Corp), the web-based Tau-U calculator accessible via Single Case Research [72], and R (version 1.4; R Foundation for Statistical Computing) [73] and separately for the primary and secondary outcomes.

To prepare the data for analysis, we will score the primary outcome of physical activity as the daily average of total activity counts per hour. The secondary outcome of daily self-control will be scored as the daily average of the 4 self-control items. Next, we will use the median average deviation to identify and remove outliers. The median average deviation uses the median to identify scores that deviate 3.5 times from the median as outliers using a 95% CI. It is specifically recommended for use in small-sample studies, including SCEDs [74].

As both experiments collect continuous data that are averaged on a daily level, our missing data approach primarily consists of making full use of data that are available. To illustrate, self-control will be measured in the morning and evening. If the morning data are missing, the afternoon data will be used to calculate the level of self-control for that day. If no data are available on a given day, we will use multiple imputation to impute missing data. Multiple imputation methods have recently been developed specifically for use in SCED studies and have several advantages over other missing data approaches, including retention of collected data, maintenance of the design structure of an SCED, reduction of bias, and the ability to capture and communicate uncertainty regarding imputed scores [75].

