#### Daily Self-control

To distribute questionnaires, the mobile survey distribution platform Ethica Data [60] will be used. Ethica is a web-based platform that is designed for researchers to create, modify, and distribute momentary surveys for experience sampling research. It allows researchers to obtain and view the data of the participant in real time to identify possible errors while the study is still running. Furthermore, it amplifies the ecological validity, possibilities, and reliability of frequent data collection [61]. Participants use their smartphones to complete the surveys. This reduces strain on participants as they do not have to carry with them additional study-related materials. Finally, trigger logistics help reduce participant burden by sending automatic reminders to fill out surveys [62].

Daily self-control will be measured using 2 items from the State Self-Control Scale [63] and 2 items specifically developed for this study. Participants use a 5-point slider ranging from 1 (*not at all*) to 5 (*very much*) to reflect on recent self-control experiences. All questions start with “In the past couple of hours...” Participants answer questions about decision-making (“it’s hard to make up my mind about even simple things”), subjective feelings of ego depletion (“I had less mental and emotional energy than I normally have”), goal-directed behavior (“I was able to do what I had planned”), and inhibitory control (“I was able to resist temptations”). We have previously used this questionnaire to measure daily self-control in students [64] and rephrased the items for people with SMI to improve clarity and brevity. A small pilot study with 5 patients receiving outpatient psychotherapeutic care showed that the rephrased items had high face validity, feasibility, and comprehension [65].

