#### Trait Self-control and Cognitive Control

Generalization measures assess the intervention effect on untrained tasks and are important to establish the external validity in SCEDs [36]. The SCRIBE guidelines [37] recommend that generalization measures are taken repeatedly, although not as frequently as the main outcome measures. In this study, trait self-control and cognitive control are used as generalization measures and assessed every 5 days (at least once per phase). This combination of measures is used as self-control is a multifaceted construct and it is recommended to use more than one type of measurement instrument to assess it [66].

Trait self-control is measured using the Brief Self-Control Scale (BSCS). The BSCS is a validated, brief, and psychometrically sound measure of individual differences in self-control that consists of 13 items [19,66,67]. The BSCS measures several aspects of trait self-control, including inhibitory and initiatory control [68]. Participants rate the extent to which a statement, for example, “I am good at resisting temptation,” matches them on a 5-point Likert scale ranging from 1 (*not at all*) to 5 (*very much*). A total score for self-control will be created by taking the sum of all items after recoding negatively phrased items (Cronbach α=.83-.85 [69]). Higher scores indicate higher levels of self-control, which has a medium effect on behavioral outcomes, showing criterion validity [70].

Cognitive control will be measured using the go/no-go task. This is a well-studied measure of cognitive control and has been used in previous research to assess self-control [32]. In the go/no-go task, participants are instructed to respond to target stimuli but must refrain from responding to nontarget stimuli, which requires suppressing a behavioral response. In this study, we will use average reaction time as the main parameter of cognitive control, with shorter reaction times reflecting more self-control [32,71].

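### The stated scoring rule for daily self-control does not reverse the two negatively worded items, so applied literally it can cancel, weaken or reverse a real improvement

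*Protocol article*

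**What the plan says.** The section on Daily Self-control describes the instrument: "Daily self-control will be measured using 2 items from the State Self-Control Scale [63] and 2 items specifically developed for this study". All four items share one response format ("Participants use a 5-point slider ranging from 1", not at all, up to 5, very much). In the article's order they are:

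1. decision-making: "hard to make up my mind about even simple things"
2. ego depletion: "I had less mental and emotional energy than I normally have"
3. goal-directed behavior: "I was able to do what I had planned"
4. inhibitory control: "I was able to resist temptations"

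The Overview of the Data Analysis section gives the scoring rule: "The secondary outcome of daily self-control will be scored as the daily average of the 4 self-control items". Outlier removal follows as the next step, and then the handling of missing days. Neither section reverses an item or says which end of the daily score is favourable.

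The section on Trait Self-control and Cognitive Control handles the BSCS differently. Its items are summed "after recoding negatively phrased items", and the article adds that higher totals mean more self-control.

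**The concern.** Strong agreement with items 1 and 2 signals low self-control. Strong agreement with items 3 and 4 signals high self-control. An unreversed average of the four sets the two pairs against each other. The result partly reflects a tendency to give high or low answers, and it loses the information on self-control that the pairs share.

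The daily score is the secondary outcome in both experiments. Level, trend, overlap and Tau-U in the visual analysis, the individual piecewise regressions and the SCED I multilevel model would all be run on it. Tau-U in particular counts data that improve, so it needs a score with a defined favourable direction. The Study Design section also uses the onset and duration of training effects on self-control to choose between 1, 2, 3 and 4 weeks of training for SCED II. A faulty daily score would therefore reach one input to that design decision.

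**Working it through.** The article states no figure on this point, so there is nothing to reproduce. The check applies the stated rule to the stated items.

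**Inputs.** Four items x1 to x4 in the article's order, each scored 1 to 5 (Daily Self-control). Items 1 and 2 are negative and items 3 and 4 positive, judged from their wording. The scoring rule is the average of the four (Data Analysis, Overview).

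**Two scores.**
- Literal: L = (x1 + x2 + x3 + x4)/4
- Recoded: R = [(6 − x1) + (6 − x2) + x3 + x4]/4

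**Extremes.**
- Worst pattern (5, 5, 1, 1): L = 12/4 = 3.0; R = (1 + 1 + 1 + 1)/4 = 1.0
- Best pattern (1, 1, 5, 5): L = 12/4 = 3.0; R = (5 + 5 + 5 + 5)/4 = 5.0

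The literal rule cannot tell these two patients apart.

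**Change under improvement.** Suppose each positive item rises by dp and each negative item falls by dn.
- Change in L = (2dp − 2dn)/4 = (dp − dn)/2
- Change in R = (2dp + 2dn)/4 = (dp + dn)/2

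| dp | dn | Change in L | Change in R | Effect of the literal rule |
|---|---|---|---|---|
| 1 | 1 | 0 | +1.0 | cancelled |
| 1 | 0.5 | +0.25 | +0.75 | weakened |
| 0.5 | 1 | −0.25 | +0.75 | sign reversed |
| 0 | 1 | −0.5 | +0.5 | sign reversed |
| 1 | 0 | +0.5 | +0.5 | unchanged |

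As an example of the first row, a patient moving from (4, 4, 2, 2) to (3, 3, 3, 3) stays at L = 3.0, while R goes from 2.0 to 3.0.

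**Relation between the two scores.** Over all 5⁴ = 625 possible response patterns, weighted equally, the correlation between L and R is 0. As an illustration only, assume a one-factor model in which all items have the same absolute loading λ. L then correlates 0 with the underlying trait, because the loadings sum to zero. R correlates 2λ/√(1 + 3λ²), which is 0.76, 0.89 and 0.97 for λ = 0.5, 0.7 and 0.9. The article gives no loadings; these three values are assumed to show a range.

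**The case against.** The strongest reply is that the error is read from silence. Nothing in the article says that raw answers are averaged unreversed. Reverse-keying is routine, and a condensed article may leave it to a fuller document. The authors clearly know the step, since they state it for the BSCS. The score is named self-control, and the missing-data paragraph speaks of a day's self-control level, which presupposes a direction. The questionnaire was used before in students and piloted after rephrasing, so a scoring key may exist in sources not shown here.

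Much of this stands. A reader might infer that the authors plan to average raw answers; the text neither states nor excludes that. What does not follow is that the gap is harmless. The scoring step is written out at the head of a data-preparation sequence, and for this scale it omits the operation that the same article spells out for another. The article does not say that scoring follows the earlier student study. An analyst following the sentence exactly would compute the wrong quantity.

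A reader might also infer that any true effect disappears. That is too strong: exact cancellation needs equal shifts on both item pairs, and if only the positive items move, the change is preserved.

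The reach is limited too. Activity counts are untouched. Study Objectives frames the duration question in terms of physical activity, and the immediacy criterion for SCED II phase length is not confined to self-control, so that decision is only partly exposed.

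**Conclusion.** The point holds as a defect in a stated rule for the secondary outcome. As written, the rule gives 3.0 to both the best and the worst response pattern and changes by (dp − dn)/2 where (dp + dn)/2 is wanted. The loss ranges from none (dn = 0), through partial and complete cancellation (dn = dp), to a change in the wrong direction (dn > dp). Which of these would occur depends on how the training moves each pair of items, which the article does not tell us.

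The conclusion rests on two assumptions: that the direction of each item is as its English wording indicates, and that the scoring sentence is applied literally. If the authors recode in practice, the numbers will be sound and only the text needs correcting. The document does not show that they intend otherwise, so this should not be read as a finding that the analysis will be wrong.

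**What to change.** Extend the scoring sentence in the Data Analysis Overview to say that the decision-making and ego-depletion items are reverse-scored (6 − x) before the four items are averaged, that higher values mean more self-control, and that this precedes outlier screening and imputation. The order matters because screening or imputing an unreversed daily score would act on the wrong series. The reversal may come before or after each item's morning and evening answers are averaged, since the mean of (6 − x) is 6 minus the mean of x. It must come before the four items are combined.

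The cost is one sentence and one line of code. Collection, randomization and visits do not change. Provided the item-level answers are kept, the step also applies to data already collected. It should be settled before the SCED I self-control results are used to choose the training duration for SCED II.
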